### Laboratory assays

#### Viral load

The plasma HIV-1 viral load will be determined using the commercial assay "RT-PCR Cobas Ampliprep-Cobas Amplicor" (Roche, Indianapolis, IN).

#### Flow cytometry

Mouse fluorochrome-labeled monoclonal antibodies (mAbs) against the following human molecules will be used: CD3, CD4, CD8, CD38 and HLA-DR; these antibodies and the corresponding isotype control antibodies will be from Becton Dickinson-Pharmingen (San Jose, CA). Frequency and phenotype of T-helper cells (defined as CD3+/CD4+ lymphocytes) and T-cytotoxic cells (CD3+/CD8+ lymphocytes) will be determined by three or four-color flow cytometry. For cell surface staining, 100 μL of anti-coagulated whole blood will be incubated with the corresponding specific fluorescence labelled mAbs for 20 min/RT in the dark. The erythrocytes will be lysed by incubating for 10 min with 2 mL of 1× FACS lysing solution (Becton Dickinson); then, cell suspension will be centrifuged for 5 min at 250 × g, the supernatant will be discarded and the cells will be washed twice with 2 mL of cold PBS at 250 × g/5 min. Finally, cells will be fixed with 250 μL of 2% formaldehyde.

The absolute number of the different T-lymphocyte subpopulations will be calculated on the basis of manually determined total and differential peripheral blood cell counts. For all experiments, appropriate isotype-matched control antibodies will be included. During the acquisition, 5 × 10^4 ^total cells will be analyzed. Dead cells will be gated out by forward and side scatter. Flow cytometry will be performed using the Becton Dickinson FACSORT instrument and analyzed with Cell Quest software.

#### Concentration of serum total cholesterol, transaminases and CPK

The serum concentration of total cholesterol will be measured by colorimetric enzymatic assay; the concentration of hepatic transaminases will be determined by immuno-turbidimetry, while the serum levels of CPK will be determined by a dry chemical assay.

#### Cellular cholesterol measurement

Cellular cholesterol content will be measured with a cholesterol oxidase-based fluorometric assay (Amplex Red Cholesterol Kit) from Molecular Probes (Eugene, OR). Cholesterol content of cells will be normalized to total cellular protein.

Assay to evaluate the adhesive function of LFA-1/ICAM-1: HIV-1 binding to immunoadhesins will be measured in virus capture assays carried out as previously described [23]. High protein-binding 96-well plates (Costar, Cambridge, MA) will be coated with goat anti-human IgG (Fc specific) at 4°C overnight (100 *μ*L/well, 10 *μ*g/mL in 50 mM Tris, pH 9.5). Supernatants will be removed and the plates will be then blocked by adding 200 *μ*L of 3% heat-inactivated bovine serum albumin in PBS to the wells for 1 hr at 37°C. After washing the wells with PBS, 100 *μ*L of supernatants containing ICAM-Ig or VCAM-Ig (6 to 10 mg/mL) will be added to the wells for 1 hr at 37°C. The wells will be washed with cRPMI before adding 100 *μ*L of cell-free virus (20 to 40 ng of p24 per mL) and incubating the plates for 1 hr at 37°C. The wells will be washed three times with cRPMI and 1% Triton X-100 in PBS will be then added to the wells to lyse bound virus. Virus quantitation will be carried out by p24 ELISA on the lysates.

#### Rho activation assay

The Rho activation assay will be performed as described [16]. Briefly, 3 × 10^6 ^peripheral blood mononuclear cells (PBMCs) will be incubated with HIV-1 stocks; then, PBMCs will be washed with ice-cold PBS and lysates will be prepared using Rho activation assay kits (Upstate Biotechnology). GTP-bound Rho will be precipitated with RBD agarose beads, and measured in pellets by Western blot with specific antibodies, using crude cell extracts for normalization.

### Biostatistical considerations

Primary hypothesis: The use of lovastatin (40 mg/day during one year) compared with placebo in HIV-1-infected individuals who are naïve for HAART, should result in a reduction of 50% or higher in viral load and an increase of 20% or higher in CD4 T cell count.

Documentation of outcome and follow-up: Primary and secondary outcome measures will be documented by investigators and research assistants masked to the subject's intervention group assignment.

Sample size and power: Based on a pilot test performed on 40 patients treated at the infectious diseases service, Hospital Universitario San Vicente de Paul (Medellin, Colombia), the baseline values for the primary and secondary outcome measures are as follows:

Mean viral load = 55,000 copies/mL; SD = 80,000 copies/mL

Mean CD4+ T cell count = 500 cells/mL; SD = 180 cells/mL

These outcomes, determined 6 and 12 months after the intervention, are longitudinal data with correlated measurements, and they need special considerations for calculation of power and sample size. In addition to the usual requirements of type I error, type II error, variation measurement and meaningful difference to be detected in longitudinal studies, it is necessary to know the number of repeated observations and an estimate of the correlation among them. The meaningful difference may be expressed as a time-averaged difference in response between groups. Assuming a fixed correlation of 0.8 among the three different measures of viral load, and a time-average difference of 50% between groups (i.e., a decrease of 22,500 copies/mL from the baseline value), with an alpha error of 0.05 and a beta error of 0.2, the sample size required is 55 patients per group. This sample size has more than 90% power to detect an increase of at least 20% in the baseline CD4+ T cell count. There will be not corrections for losses to follow-up or non-adherence, as the study is intended as a pilot phase II trial.

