### Study Population

One hundred and ten (110) chronically HIV-1 infected patients without antiretroviral treatment.

The inclusion criteria will be the following:

- Asymptomatic HIV-1 positive individuals, with age ≥ 18 years, who are HAART naive

- HIV-1 infection confirmed by: a) any positive western blot at least six months before admission to the study; or b) within the last six months by a western blot that includes the p31 and p66 bands

- Detectable viral load but less than 100,000 copies/mL

- CD4+ T cell count ≥ 350 cells/μL

The exclusion criteria will be the following:

- Inability or unwillingness of patients to give written informed consent

- Main residence outside Medellin and its metropolitan area, or any indication of difficulties in the follow-up period

- Participation in other clinical trials

- Evidence that the patient will exhibit low adherence to intervention and follow-up (Morisky-Green test)

- Pregnancy or breastfeeding

- Any type of antiretroviral treatment before admission to the study, and therapy with lipid-lowering drugs during the last six months

- Antecedents of allergy, contraindications or intolerance to statins

- Patients receiving medications which can generate relevant interactions with lovastatin: clarithromycin, erythromycin, azithromycin, itraconazole, ketoconazole, nefadozone, cimetidine, rifampin, phenobarbital, carbamacepin, phenitoin, gemfibrozil.

- Unwillingness to avoid the consumption of Citrus paradise (grapefruit juice) or Saint John's Wort (Hypericum)

- Chronic active hepatitis (B or C)

- Any hepatocellular disease, indicated by elevation of liver enzymes (AST or ALT) more than twice the upper limit of reference values

- Renal failure, indicated by serum creatinine ≥ 2 mg/dL

- Myopathy, indicated by an elevation of creatine phosphokinase (CPK) more than five times the upper limit of reference values

- Infection or acute disease that requires inpatient treatment

- Active substance-related disorders.

- Medical indication for using lipid-lowering drugs

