### Study outcomes

The efficacy of lovastatin to control HIV-1 replication allowing an improved immune reconstitution will be determined by primary and secondary outcomes. The primary outcome will be the viral load measured as RNA copies per mL of peripheral blood, and the secondary outcome will be the CD4 T-cell count measured as cells per μL of peripheral blood; both determined at enrolment, and 6 and 12 months after the intervention.

The tertiary or exploratory outcomes will be the following (determined at enrolment, and 6 and 12 months of interventions, unless indicated otherwise):

- Absolute number per μL of peripheral blood of CD8+ T lymphocytes and the CD4/CD8 ratio

- Basal expression of immunological activation markers (CD38 and HLA-DR) on CD4+ and CD8+ T lymphocytes

- Concentration of total serum cholesterol

- Concentration of cellular cholesterol

- Functional activity of LFA-1 and ICAM-1

- Activity of Rho GTPases

- Monthly frequency and type of: infections, non-infectious AIDS defining diseases, hospitalizations

- Mortality due to an HIV-1/AIDS related cause

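### The baseline viral load SD of 80,000 copies/mL used for the sample size cannot occur under the trial's own entry limit of less than 100,000 copies/mL

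*Protocol article*

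**What the plan says.** In the Protocol article, the inclusion criteria under Study Population require "Detectable viral load but less than 100,000 copies/mL". Under Biostatistical considerations, the planning figures come from a pilot: "Based on a pilot test performed on 40 patients treated at the infectious diseases service". They are introduced with the words "the baseline values for the primary and secondary outcome measures are as follows", and for viral load they read "Mean viral load = 55,000 copies/mL; SD = 80,000 copies/mL". The pilot patients are not said to have met the viral load limit.

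The same paragraph goes on: "Assuming a fixed correlation of 0.8 among the three different measures of viral load", a time-averaged difference of 50% expressed as "a decrease of 22,500 copies/mL from the baseline value", alpha 0.05 and beta 0.2, giving 55 patients per group. Study Outcomes puts the primary outcome on the untransformed scale ("The primary outcome will be the viral load measured as RNA copies per mL of peripheral blood"), with viral load and CD4 count "both determined at enrolment, and 6 and 12 months after the intervention".

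**The concern.** A variable confined to a range cannot have an SD above half the width of that range. For 0 to 100,000 the limit is 50,000, and the plan uses 80,000. The planning mean and SD therefore come from a group that includes at least one patient whom the trial would exclude.

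Both inputs that set the power are affected. The SD of eligible patients at baseline must be smaller. Their mean must be smaller too, because every pilot patient removed for exceeding 100,000 lies above the pilot mean. A 50% effect is then fewer copies/mL than the plan assumes. The correlation may also differ in the restricted group. The claim of 80% power with 55 per group is thus made for a population other than the one defined by the entry criteria.

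**Working it through.** **Inputs.** From Study Population: baseline viral load above 0 and below 100,000. From Biostatistical considerations: n = 40, mean 55,000, SD 80,000, correlation 0.8, three measures, difference 22,500, alpha 0.05 (two-sided assumed), power 0.80, 55 per group.

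**1. The plan's own figure.** With SD 80,000 and difference 22,500,

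n per group = 2 × (1.960 + 0.842)² × (80,000/22,500)² × f = 198.5 × f.

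- Time-averaged difference over three measures, as the text describes: f = (1 + 2 × 0.8)/3 = 0.867, so n = 172.
- Mean of two follow-up measures minus baseline: f = 0.9 + 1 − 1.6 = 0.30, so n = 60.
- Mean of two follow-up measures adjusted for baseline (ANCOVA): f = 0.9 − 0.64 = 0.26, so n = 52.

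The described formula does not give 55. The two baseline-adjusted versions lie on either side of it. That is a separate defect. What matters here is that the variants that come near 55 all use the SD of 80,000.

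**2. Ceiling on the baseline SD.** For values in [0, 100,000] with mean μ, SD ≤ √(μ × (100,000 − μ)).

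- At μ = 55,000: √(55,000 × 45,000) = 49,749. As a sample SD with n = 40 this is 49,749 × √(40/39) = 50,383.
- At any mean: 50,000, or 50,637 as a sample SD.

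The planning SD is 80,000/49,749 = 1.6 times the ceiling. No distributional assumption is involved.

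**3. Highest possible mean of the eligible pilot patients.** Take the printed mean and SD as exact.

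- Sum of values: 40 × 55,000 = 2.2 million.
- Sum of squares: 39 × 80,000² + 40 × 55,000² = 3.706 × 10¹¹.

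The eligible mean is highest when one patient, at x, is above the cap and the other 39 are spread as widely as the cap allows (at 0 or 100,000). The squares of those 39 then sum to 100,000 × (2,200,000 − x). Solving x² + 100,000 × (2,200,000 − x) = 3.706 × 10¹¹ gives x ≈ 441,300. The other 39 average (2,200,000 − 441,300)/39 ≈ 45,100, and half of that is 22,550.

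So 27,500 cannot be a 50% reduction in the eligible pilot patients, and 22,500 can be one only very near this extreme. If the other 39 were all equal, the outlier would be about 548,000, their mean about 42,400 and half of it about 21,200.

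**4. Effect on the required number**, with the time-averaged formula (f = 0.867):

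| Case | SD | Difference | n per group | Power at 55 |
|---|---|---|---|---|
| As printed | 80,000 | 22,500 | 172 | 0.35 |
| Ceiling SD, stated difference | 49,749 | 22,500 | 67 | 0.72 |
| Ceiling SD, half of 55,000 | 49,749 | 27,500 | 45 | 0.88 |
| Lognormal cut at 100,000 (assumed) | 23,900 | 16,300 | 30 | 0.97 |

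The last row assumes that the pilot is lognormal with the printed mean and SD. About 14% of patients then lie at or above 100,000. The rest have mean about 32,600 and SD about 23,900, so a 50% effect is about 16,300. With baseline adjustment, the second row falls to 24 (change) or 20 (ANCOVA) and the last to 11 or 9.

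**The case against.** Four points can be made on the plan's behalf.

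- **The cap applies at enrolment only.** Values at 6 and 12 months may exceed 100,000, so an SD above 50,000 is possible at those visits. This stands, and the ceiling is proved for baseline alone. But the plan labels 80,000 a baseline figure and gives no separate follow-up SD.
- **The bound proves only one over-cap patient.** A single value near 548,000 among 40 would produce the printed mean and SD. This stands too. A reader might infer that much of the pilot was ineligible, but the documents do not show that; the 14% rests on the assumed lognormal.
- **The mismatch may be conservative.** A reader might infer that the trial is too small. The documents do not support that: for a percentage effect, n depends on SD/mean. This ratio is 80,000/55,000 = 1.45 as printed and 23,900/32,600 = 0.73 in the lognormal illustration, where n falls to 30. The 67 at the ceiling SD needs nearly every patient at 0 or 100,000.
- **The stated 22,500 is half of 45,000, a mean that the cap allows.** This is true of the cap alone. Combined with the pilot's own mean and SD, a mean of 45,000 is reachable only at the edge of what is possible (step 3).

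A reader might also extend the argument to CD4, since a normal distribution with mean 500 and SD 180 puts about 20% below the entry limit of 350. That does not follow. CD4 has a floor and no ceiling, and 350 plus a right-skewed excess with mean 150 and SD 180 gives exactly the printed figures. No bound is broken, and normality is not stated in the plan.

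**Conclusion.** The point holds for viral load. The baseline SD of 80,000 is 1.6 times the largest value that eligible patients with that mean could have, so at least one pilot patient was above the entry limit. This rests only on the printed figures. The eligible mean is at most about 45,100 if the printed mean and SD are exact, so the target of 50% in absolute copies/mL is overstated, except possibly at an extreme.

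The 80% power stated for 55 per group does not describe the enrolled population. The direction of the error is unknown: across the cases that respect the cap, the described formula needs 30 to 67 per group. The low end assumes a truncated lognormal, the high end assumes the ceiling SD, and neither allows for a larger SD at follow-up. The plan should correct these inputs, but this point gives no ground for calling the trial underpowered.

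**What to change.** Recompute the mean, SD and correlation from the pilot patients who meet the entry criteria (viral load below 100,000 copies/mL and CD4 count at least 350 cells/μL). State how many of the 40 remain. Allow for follow-up values above the cap, for instance by giving the power over a range of follow-up SDs. Then restate the 50% difference in copies/mL from the eligible mean, name the formula used, and report the power that 55 per group gives.

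The cost is a re-tabulation of existing pilot data, a short sensitivity calculation and one revised paragraph. The planned 110 patients stay unchanged. If the restated power is below 80%, the paragraph should say so.

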The β coefficient obtained with this procedure for the X variable is the estimated time-averaged change in the outcome measure in the lovastatin group compared with placebo, and its p-value is given by the Wald statistic . We will use the *xt *of commands from the statistical package Stata (StataCorp, 2007: Release 10, College Station, Texas, USA) for the proposed analysis of cross-sectional time-series datasets. Specifically, the command *xtgee *will evaluate population-averaged panel-data models using GEE. Although the expectation is that randomization assists in balancing known and unknown prognostic factors in a randomized clinical trial, this assignment process is not a guarantee against the possibility that estimates of treatment effect be modified by covariate imbalance. Accordingly, the estimated time-averaged change in the outcome measure for lovastatin vs. placebo will be adjusted by the most important prognostic factors (baseline CD4+ T cell count, baseline viral load, and adherence to the treatment) considered as additional independent variables in the same GEE model.

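### The sample-size basis counts the enrolment value among the three viral-load measures and the analysis plan does not keep it out of the GEE response; if it is included, the treatment coefficient estimates two thirds of the effect

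*Protocol article*

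**What the plan says.** - **Schedule.** Study outcomes in the protocol article says of viral load and CD4 count: "both determined at enrolment, and 6 and 12 months after the intervention". That is one measurement before treatment and two after it.
- **Sample-size basis.** Biostatistical considerations sets up the calculation with "Assuming a fixed correlation of 0.8 among the three different measures of viral load, and a time-average difference of 50% between groups". It gives that difference as 22,500 copies/mL.
- **The same paragraph, differently.** It introduces the outcomes with: "These outcomes, determined 6 and 12 months after the intervention, are longitudinal data with correlated measurements". That describes two measures.
- **Analysis.** The Analysis plan makes the time-averaged group difference the main interest. It fits an exchangeable GEE with robust standard errors and reads the coefficient for the intervention as "the estimated time-averaged change in the outcome measure in the lovastatin group compared with placebo". The patient's response vector has an unspecified number of observations that are not tied to visits. No treatment-by-time term is described.
- **Adjustment.** The last paragraph of the Analysis plan adds baseline viral load, baseline CD4 count and adherence as independent variables in the same model. It does not say whether the unadjusted or the adjusted coefficient is primary.

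**The concern.** A time-averaged treatment difference should average over visits at which treatment can have acted. Randomisation makes the expected group difference at enrolment zero. If that visit enters the average with equal weight, the result is pulled toward no effect by a fixed fraction, however large the trial.

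The text leads toward this. Only three measurements are scheduled, the planning average is built on three, and the analysis targets the same kind of average with a single coefficient. Yet the same document also describes the outcomes as follow-up values and uses baseline as a covariate. The definition of the primary effect is therefore contradictory. At stake are the size of the reported effect and, if the unadjusted coefficient is primary, the power of the trial.

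**Working it through.** **Inputs.** Biostatistical considerations gives "Mean viral load = 55,000 copies/mL; SD = 80,000 copies/mL", correlation ρ = 0.8, alpha 0.05, power 80% and 55 per group. Two-sided alpha is assumed, since sidedness is not stated. The stated difference is 22,500; half of 55,000 is 27,500. That mismatch is a separate matter, so both values are carried through as D. No dropout is assumed.

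**Step 1: the plan's own figure.** For the average of m equally correlated measures,

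n per group = 2(1.96 + 0.842)² × SD² × f / D², with f = [1 + (m − 1)ρ]/m.

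For m = 3, f = (1 + 1.6)/3 = 0.867. This gives 116 per group for D = 27,500 and 172 for D = 22,500 (one-sided: 91 and 136). The stated 55 is not reproduced.

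**Step 2: what the coefficient estimates.** With balanced data, a single treatment term and exchangeable correlation, the unadjusted coefficient is the difference in patient means. With enrolment in the response and effect D at months 6 and 12:

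(0 + D + D)/3 = 2D/3

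- D = 22,500 gives 15,000.
- D = 27,500 gives 18,333, which is 33% of 55,000 instead of 50%.

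**Step 3: unadjusted power at 55 per group.** Power = Φ(effect/SE − 1.96), with SE = 80,000 × √(2f/55).

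| Response visits | f | SE | Power, D = 22,500 | Power, D = 27,500 |
|---|---|---|---|---|
| Enrolment, 6, 12 (effect 2D/3) | 0.867 | 14,202 | 18% | 25% |
| 6 and 12 (effect D) | (1 + 0.8)/2 = 0.900 | 14,473 | 34% | 48% |

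For 80% power, the first row would need 387 or 260 per group and the second 179 or 120. For CD4 (SD 180, difference 100), unadjusted power falls from 87% with months 6 and 12 to 55% with all three visits.

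**Step 4: with the enrolment value as covariate.** For months 6 and 12, f = (1 + ρ)/2 − ρ² = 0.90 − 0.64 = 0.26, so SE = 80,000 × √(0.52/55) = 7,779. Power is 82% for D = 22,500 and 94% for D = 27,500. If enrolment is also kept in the response, its residual given itself is zero. The estimate and its SE are then both multiplied by 2/3, so the Wald ratio and the power do not change.

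**Step 5: simulation.** Exchangeable GEE with robust SE, 55 per group, D = 27,500, normal data, 300 runs, in thousand copies/mL:

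| Model | Mean coefficient | SE | Power |
|---|---|---|---|
| Three visits, unadjusted | −18.8 | 13.9 | 30% |
| Three visits + baseline | −18.6 | 5.1 | 94.7% |
| 6 and 12, unadjusted | −28.0 | 14.2 | 53% |
| 6 and 12 + baseline | −27.8 | 7.6 | 94.7% |

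The unadjusted powers carry a Monte Carlo error of 2.5 to 3 percentage points. A separate run of 4,000 gave 26% for the first row.

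**The case against.** The strongest reply is that nothing in the Analysis plan makes enrolment a response. The three-measure phrase is an assumption about correlation for sample size. The same paragraph speaks of months 6 and 12, and listing baseline as an independent variable is the usual form of a GEE with post-baseline responses. The stated 55 also does not come from an equal average of three measures. Two follow-ups with a baseline covariate at 22,500 need 52 to 53 per group, which is close. A change score or a slope at 27,500 needs 54 to 55, so the intended method cannot be recovered. A condensed article may also leave the list of response visits to a fuller document.

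Much of this stands, and it rules out some stronger readings that a reader might infer:

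- **That the coefficient is certainly diluted.** This is conditional, because the response visits are never named.
- **That power drops from 94% to 25%.** That comparison changes two things at once, the visits and the covariate. Like for like, unadjusted power goes from 48% to 25% (or 34% to 18%), and adjusted power does not move.
- **That a diluted estimate would fail the trial's criterion.** The 50% figure is a hypothesised effect. The Analysis plan judges by a Wald p-value and sets no threshold for the estimate.
- **That dilution explains the 55 per group.** It does not (Step 1).

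The reply does not remove the contradiction. The article itself states three measures as the basis of the time-averaged difference, and with this schedule the third can only be the pre-treatment one. That is a stated planning basis that conflicts with other statements in the article, so it is more than an omitted detail.

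**Conclusion.** The concern holds in conditional form. The sample-size basis counts the enrolment value, while other sentences treat the outcomes as follow-up values and baseline as a covariate. If the three measures form the GEE response with one treatment coefficient, the reported effect is understated by one third. Power is lost only in the unadjusted model.

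The one-third figure assumes an equal effect at months 6 and 12 and complete data. The powers also assume SD 80,000, correlation 0.8 and two-sided alpha 0.05, and the adjusted figures use only the enrolment value of the outcome as covariate. Because the contradiction lies in the definition of the primary effect and removing it costs almost nothing, it should be settled before the data are unblinded.

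**What to change.** - In the Analysis plan, state that the GEE response consists of the month 6 and month 12 values only, with the enrolment value of the same outcome as a covariate (viral load for the viral-load model, CD4 for the CD4 model).
- Name this baseline-adjusted model as primary and read its treatment coefficient as the average difference over the two follow-up visits.
- In Biostatistical considerations, replace the three-measure basis with two post-baseline measures plus a baseline covariate, and recompute. Under the stated SD and correlation, 55 per group gives about 82% power for 22,500 and 94% for 27,500. The paragraph must also settle which of these two differences is meant.

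The cost is a wording change and a short recalculation. No visits, samples or patients are added.

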### Interim monitoring

An independent DSMB comprising three members with expertise in statistics, epidemiology and infectious diseases will be responsible for the interim monitoring process. The statistician at the Data-Coordinating Center will be the only person with access to the full database and he will provide the required information, both overall for the interim quality assurance and specific by treatment group (efficacy and safety) exclusively for the DSMB. The first interim monitoring will be conducted when the study participants complete six months of evaluation. The second interim analysis will be conducted when all the patients complete nine months of evaluation. Stopping guidelines for efficacy monitoring will be determined for the primary and secondary outcomes according to the modified O'Brien-Fleming procedure. With this procedure, the values for statistical significance are 0.0006 and 0.0151 in the first (α_1_) and second (α_2_) interim analyses, respectively, for a final significance (α) of 0.0471. Stopping guidelines for safety are left at discretion of the DSMB, with an expected rate of adverse events (hepatic or muscle enzymes elevations) less than 1%. Stopping guidelines regarding futility are not considered and this was agreed in a meeting with the DSMB.

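### The viral-load sample size does not follow from its stated inputs: 22,500 copies/mL is 41%, not 50%, of the mean, and the calculation described gives 116 or 172 per group, not 55

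*Protocol article*

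**What the plan says.** All the design inputs are in the Protocol article, Biostatistical considerations. A pilot in 40 patients supplies "Mean viral load = 55,000 copies/mL; SD = 80,000 copies/mL". The primary hypothesis is a viral-load reduction of at least 50%. The calculation is framed as a time-averaged difference between groups: "Assuming a fixed correlation of 0.8 among the three different measures of viral load", with "a time-average difference of 50% between groups (i.e., a decrease of 22,500 copies/mL from the baseline value"), and "with an alpha error of 0.05 and a beta error of 0.2, the sample size required is 55 patients per group". No allowance is made for losses or non-adherence.

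Three other places bear on how to read this:

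- Study outcomes lists the viral-load and CD4 measurements as "both determined at enrolment, and 6 and 12 months after the intervention". Of the three measures, one is therefore pre-treatment and two are post-treatment.
- Analysis plan describes a GEE model with exchangeable correlation, and adds baseline viral load as a covariate.
- Interim monitoring plans two interim analyses, "for a final significance (α) of 0.0471".

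**The concern.** Two things do not fit. First, the percentage and the absolute difference describe different targets. Required sample size varies with the inverse square of the difference, so the choice between them changes any required number by (27,500/22,500)² = 1.49.

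Second, the paragraph gives the inputs of the standard formula for a time-averaged difference, but that formula does not return 55 for either target.

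At stake is how the primary result is read. If the trial finds no difference, a reader needs to know what effect it could have detected, and with what probability. The text supports neither a single target nor the stated 80% power.

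**Working it through.** **Inputs** (Biostatistical considerations): mean 55,000; SD 80,000; correlation ρ = 0.8; three measures; alpha 0.05; power 80%; 55 per group. The text does not say whether alpha is one- or two-sided; two-sided is assumed.

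**Step 1: the target.** 0.50 × 55,000 = 27,500. Conversely, 22,500 / 55,000 = 40.9%. (22,500 would be half of 45,000.)

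**Step 2: the calculation as described.**

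n per group = 2(1.960 + 0.842)² × SD² × V / d², where V = [1 + (m − 1)ρ] / m.

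With m = 3 and ρ = 0.8, V = 2.6/3 = 0.8667.

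- d = 27,500: n = 115.1, so 116.
- d = 22,500: n = 171.99, so 172.

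Power at 55 per group is Φ(d/SE − 1.960), with SE = 80,000 × √(2 × 0.8667/55) = 14,202.

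- d = 27,500: Φ(1.936 − 1.960) = 49%.
- d = 22,500: Φ(1.584 − 1.960) = 35%.

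If only the two follow-up measures count as outcomes, still without baseline, V = 0.90 and n is 120 or 179. A one-sided alpha of 0.05 with three measures gives 91 or 136. None of these is 55.

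**Step 3: one baseline and two follow-ups, with baseline used.**

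- ANCOVA: V = (1 + ρ)/2 − ρ² = 0.90 − 0.64 = 0.26.
- Change score: V = (1 + ρ)/2 + 1 − 2ρ = 0.90 + 1 − 1.6 = 0.30.

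| Method, ρ = 0.8, two-sided 0.05 | n for 22,500 | Power at 55 | n for 27,500 | Power at 55 |
|---|---|---|---|---|
| ANCOVA | 52 | 82% | 35 | 94% |
| Change score | 60 | 77% | 40 | 91% |

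For 22,500 these bracket 55, but neither equals it. Results closer to 55 need a departure from the stated inputs. A change score with a single follow-up and 27,500 gives 54 (55 at alpha 0.0471). A change score with three follow-ups and 22,500 gives 53. ANCOVA with two follow-ups and 22,500 gives 53 at alpha 0.0471.

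**Step 4: dependence on the correlation** (ANCOVA, two follow-ups, 55 per group, two-sided 0.05).

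| ρ | V | Power, 22,500 | Power, 27,500 |
|---|---|---|---|
| 0.8 | 0.26 | 82% | 94% |
| 0.7 | 0.36 | 69% | 85% |
| 0.5 | 0.50 | 55% | 72% |

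Moving from alpha 0.05 to 0.0471 matters little: at ρ = 0.8 and 22,500, power goes from 82.4% to 81.8%.

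**The case against.** The strongest reply is that Step 2 is the wrong model of this trial. One of the three measures is taken at enrolment, the effect is worded as a fall from baseline, and the GEE model adjusts for baseline viral load. Once baseline is used, 55 per group has 77% to 82% power for the printed 22,500, close to the 80% claimed. This stands. A reader might infer from Step 2 that the trial's true power is only 35% to 49%; the document does not support that. The reply does not rescue the paragraph, however. The sample-size text never mentions baseline adjustment, and with three measures and alpha 0.05 the baseline-using formulas give 52 or 60 (22,500) and 35 or 40 (27,500). The route to 55 can be guessed at but is not documented.

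The entry limit is a further reason not to read 35% to 49% as actual power. Study Population requires viral load below 100,000 copies/mL, so the baseline SD of enrolled patients cannot exceed 50,000. The pilot SD of 80,000 cannot describe them at enrolment.

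A reader might also infer that the claim of more than 90% power for CD4 is wrong, since the unadjusted formula with ρ = 0.8 gives 88% (difference 100, SD 180). That does not hold. The 0.8 is stated only for viral load. The same formula gives 90.3% at ρ = 0.7, and using baseline at ρ = 0.8 gives more than 99.9%.

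Finally, a journal article may leave the formula to the full protocol. That is accepted: the complaint is not that a formula is missing, but that the printed figures disagree with one another.

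**Conclusion.** The point holds in this limited form. The contradiction between 50% and 22,500 is certain and rests only on the article's own numbers. That 55 does not follow from the calculation described is also firm: the shortfall is about twofold (116) or threefold (172), assuming a two-sided test.

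What cannot be concluded is that 110 patients are too few. At correlation 0.8 and SD 80,000, a baseline-adjusted analysis of two follow-ups has power near or above 80% for either target. That conclusion depends heavily on the correlation, for which the article gives no source, and it makes no allowance for losses. The defect is in the stated target and its justification, and it should be corrected because it governs how a null result is interpreted.

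**What to change.** Keep 110 patients, and change the text as follows:

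1. Reconcile the target: either correct 22,500 to 27,500 copies/mL, or state that the target difference is 41% and align the primary hypothesis with it.
2. Replace the described calculation with one that matches the analysis, namely the mean of months 6 and 12 adjusted for baseline viral load. Name the formula, whether alpha is one- or two-sided, and the final alpha used.
3. Report viral-load power at 55 per group over correlations 0.5 to 0.8 instead of at 0.8 alone.

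The CD4 power statement need not be withdrawn on this ground. The cost is wording in the protocol and analysis plan. The single 80% figure is replaced by a range that depends openly on the assumed correlation.
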